### Sample size

2.7

This trial aims to determine whether HT080 is superior to placebo for reducing the change in IPSSs from baseline to week 12. The sample size has been estimated based on the results of a previous study that had shown an extract of *Ganoderma lucidum* improves IPSSs.^[26]^ Because the standard deviations for changes in IPSSs are not present in this literature, they have been approximated using the confidence intervals and significant probabilities of pre- and post-treatment values for IPSSs. The difference in the mean change in IPSSs between the HT080 and control groups is hypothesized to be 1.18 and the standard deviation is hypothesized to be 1.88. A total of 80 participants, 40 in each group, are required to achieve 80% power with a two-sided significance level of 5%. Considering a dropout rate of 20%, a total of 100 participants (50 in each group) will be enrolled.

### Statistical analysis

2.8

Efficacy outcomes will be assessed in both full analysis and per-protocol sets. The full analysis set will consist of all randomized participants who are subjected to at least one efficacy evaluation after being administered at least one dose of the study product without failing major inclusion criteria. The per-protocol population will include participants in the full analysis population who complete this trial without major protocol deviations that affect the study results. Safety outcomes will be analyzed in the safety set, which will include all randomized participants who receive at least one dose of study product. Missing values will be handled by the last observation carried forward method.

Continuous variables will be presented with mean, median, standard deviation, and range (min and max), and categorical variables will be presented as frequency and percentage. Continuous variables between the two groups will be compared by the two-sample *t* test or Wilcoxon rank sum test, depending on the normality of distribution, and the differences before and after treatment in each group will be analyzed using a paired t-test or Wilcoxon signed-rank test. Categorical variables will be compared using the chi-square test or Fisher exact test. For primary and secondary efficacy variables, analysis of covariance will be performed to compare the change from baseline to weeks 6 and 12 between the groups while adjusting for baseline values. If necessary, subgroup analysis stratified by baseline characteristics (e.g., age) will be performed. Adverse events will be coded by System Organ Class and Preferred Terms from the Medical Dictionary for Regulatory Activities. Probability values of <.05 with two-tailed tests will be considered significant. The statistical analysis will be performed with SPSS Statistics software version 25 (IBM, Chicago, IL). There will be no interim analyses.

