**Methods/design::**

A double-blind, randomized, placebo-controlled, two-arm parallel group trial will be conducted in men with moderate LUTS/BPH. A total of 100 eligible men aged 40 to 75 years with an International Prostate Symptom Score of 8 to 19 will be randomized in a 1:1 ratio and receive either HT080 (500 mg) or placebo twice a day for 12 weeks. All participants will be evaluated for efficacy and safety at baseline and weeks 6 and 12. The primary endpoint is the change in International Prostate Symptom Score between baseline and week 12. The secondary efficacy variables are uroflowmetry parameters (maximal urinary flow rate and post-void residual volume), serum prostate-specific antigen, testosterone, and dihydrotestosterone levels, the International Index of Erectile Function score, and participant-reported global response assessment scores. The safety assessments include adverse events, laboratory tests results, vital signs, and physical examination.

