### Outcome measures

2.6

The Korean IPSS questionnaire will be used to assess the primary endpoint. The IPSS, which has been used for decades to assess the severity of LUTS/BPH, contains seven questions on voiding symptoms (incomplete emptying, intermittency, weak stream, and straining) and storage symptoms (frequency, urgency, and nocturia).^[22]^ Each item is scored 0 to 5, giving a maximum total score of 35. A total score of 0 to 7 indicates mild symptoms, 8 to 19 indicates moderate symptoms and 20–35 indicates severe symptoms. Participants will complete the IPSS questionnaire at screening, baseline, and weeks 6 and 12. The primary efficacy endpoint is the change in IPSS at week 12 from the baseline.

As the secondary outcomes, uroflowmetry parameters (maximal urinary flow rate and post-void residual volume) and serum prostate-specific antigen, testosterone, and dihydrotestosterone levels will be measured at screening and weeks 6 and 12. Global response assessment will be completed by participants at weeks 6 and 12 using a five-point scale (markedly worsened, worsened, unchanged, improved, and markedly improved). It has been reported that 70% of BPH patients has an associated erectile dysfunction.^[23]^ Participants will complete the International Index of Erectile Function questionnaire, a multi-dimensional self-report instrument widely used to evaluate male sexual function,^[24,25]^ at baseline and weeks 6 and 12. The safety outcome measures include adverse events, laboratory tests (hematology, biochemistry, and urinalysis) results, vital signs, and physical examination.

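### The baseline-adjusted ANCOVA set for the secondary efficacy variables cannot be computed for the global response assessment, and the tests named for categorical data ignore the order of its grades

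*Protocol article*

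**What the plan says.** The abstract's Methods/design paragraph closes its list of secondary efficacy variables with "the International Index of Erectile Function score, and participant-reported global response assessment scores". Outcome measures (2.6) gives the timing and format: "Global response assessment will be completed by participants at weeks 6 and 12 using a five-point scale", with the grades "markedly worsened, worsened, unchanged, improved, and markedly improved". The other secondary variables in 2.6 each have a pre-treatment value. The uroflowmetry measures, prostate-specific antigen, testosterone and dihydrotestosterone are measured at screening, and the erectile function questionnaire is completed at baseline.

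Statistical analysis (2.8) contains three rules that could bear on the assessment:

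- Efficacy variables: "For primary and secondary efficacy variables, analysis of covariance will be performed to compare the change from baseline to weeks 6 and 12", with each variable's own baseline value as the covariate.
- Continuous variables: "Continuous variables between the two groups will be compared by the two-sample" t test or the Wilcoxon rank sum test, depending on normality.
- Categorical variables: "Categorical variables will be compared using the chi-square test or Fisher exact test".

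No sentence says which of these applies to the global response assessment.

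**The concern.** The ANCOVA rule needs a change from baseline as the response and a baseline value as the covariate. The global response assessment supplies neither. Its first rating is at week 6, and each rating already expresses change since before treatment. The rule is nevertheless stated for the secondary efficacy variables as a class.

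With that rule unusable, the rule that matches a set of verbal grades is the categorical one. Chi-square and Fisher exact give the same p-value however the five columns are arranged. They spend up to four degrees of freedom on any kind of difference, whereas the question is whether HT080 moves men towards improvement.

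Two things are at stake. The test for this endpoint could be settled after the data are seen, with several candidates that may disagree at this sample size. And the most literal choice is inefficient if the treatment produces a consistent shift.

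**Working it through.** **1. The plan's own figure.** Sample size (2.7) gives a difference of 1.18, SD 1.88, two-sided 5% and 80% power.

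n per arm = 2 × (1.960 + 0.842)² × (1.88 / 1.18)² = 39.85, rounded up to 40. Power at 40 per arm is 80.15% by the normal formula (79.2% by the t distribution). Enrolment is 80 / (1 − 0.20) = 100. The stated sample size reproduces, and nothing below affects it.

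**2. Can the ANCOVA be computed?**

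| Needed by the ANCOVA rule in 2.8 | Available for the global response assessment (2.6) |
|---|---|
| Value at week 6 or 12 | Yes |
| Baseline value, as covariate | No; rated at weeks 6 and 12 only |
| Change from baseline, as response | No; the grade is itself a rating of change |

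It cannot. The problem is confined to this variable, because all the others have a screening or baseline value.

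**3. Cost of ignoring the order.** The article gives no distribution for this outcome, so the inputs here are assumptions. Placebo percentages, from markedly worsened to markedly improved:

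- A: 2 / 8 / 50 / 35 / 5
- B: 5 / 15 / 40 / 30 / 10
- C: 1 / 4 / 65 / 28 / 2

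The treated arm follows a proportional-odds shift: each cumulative odds of being at or below a grade is divided by the odds ratio (OR). Example, A with OR 3: the odds of unchanged or worse are 0.60 / 0.40 = 1.5 on placebo and 1.5 / 3 = 0.5 on treatment, a probability of 0.333. Improved or better therefore goes from 40% to 66.7%.

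Arm sizes are the article's own 40 (evaluable) and 50 (enrolled). There were 20,000 simulated trials per scenario (Monte Carlo standard error at most √(0.25 / 20,000) = 0.35 points), tested at two-sided 5%. The tests were:

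- Pearson chi-square: Σ (observed − expected)² / expected, with degrees of freedom equal to occupied grades minus 1.
- Wilcoxon rank sum on midranks: z = (W − n(N + 1)/2) / √V, with N = 2n and V = (n²/12) × [(N + 1) − Σ(t³ − t) / (N(N − 1))], where t is the total in each grade.

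Rejection rates, as ranges over A to C; the gap is taken within each distribution:

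| OR | Per arm | Chi-square | Wilcoxon | Gap (points) |
|---|---|---|---|---|
| 1 | 40 | 2.4–4.4% | 4.7–4.9% | – |
| 1 | 50 | 2.8–4.3% | 5.0–5.1% | – |
| 2 | 40 | 17–21% | 33–39% | 16–18 |
| 2 | 50 | 22–27% | 41–47% | 18–20 |
| 2.5 | 40 | 32–36% | 54–60% | 21–24 |
| 2.5 | 50 | 41–46% | 63–70% | 22–24 |
| 3 | 40 | 47–52% | 69–76% | 22–24 |
| 3 | 50 | 58–64% | 79–85% | 21 |
| 4 | 40 | 71–75% | 87–92% | 17–18 |
| 4 | 50 | 82–85% | 94–96% | 11–12 |

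A repeat run with a different random seed agreed to within about one point.

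**4. Does Fisher close the gap?** In distribution A with OR 3 and 40 per arm, the Fisher exact test extended to the 2 × 5 table had 53% power, against 73% for Wilcoxon. It does not.

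**The case against.** The strongest reply is that the ANCOVA sentence limits itself. It speaks of change from baseline and of baseline values, so an analyst would pass over a variable that has none and use the general rules in the same paragraph. A reader might infer from the conflict that the assessment has no possible analysis at all. The article does not support that, since two general rules remain. What stands is that the sentence names the secondary variables without exception, and nothing says which general rule takes over.

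A reader might also infer that the plan commits itself to an unordered test. It does not. The abstract speaks of "and participant-reported global response assessment scores". If the five grades are handled as scores, the continuous rule applies, and that rule already offers Wilcoxon rank sum. This is a fair reading, but the article does not state it.

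A third tempting inference is that chi-square would be invalid because the table is sparse. Under distributions A and C, at least 98% of simulated tables had more than a fifth of expected counts below 5. Under the wider-spread B this fell to roughly 30–80%, depending on effect and arm size. In either case 2.8 names Fisher exact as the alternative, and chi-square rejected at most 4.4% of the time under no effect. The weakness is in power, not in error control.

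The power comparison also assumes a proportional-odds shift, which suits a rank test; a non-monotone effect could favour chi-square. The article sets no power target for this outcome, so none is missed, and none of the stated objectives names it.

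Finally, the test for one secondary outcome is often left to a fuller document, and 2.12 says that a full protocol exists. That excuses silence. It does not excuse a stated rule that cannot be applied to a variable it covers.

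**Conclusion.** The conflict is certain from the text. Section 2.8 applies a baseline-adjusted analysis of change to the secondary efficacy variables, and 2.6 collects one of them with no baseline. No later sentence resolves which test replaces it, and the tests named for categorical data do not use the order of the grades.

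The size of the power loss is illustrative. It rests on three assumed placebo distributions and a proportional-odds shift. For odds ratios of 2 to 3 at 40–50 per arm, chi-square gives up about 16 to 24 points to a rank test. At an odds ratio of 4 with 50 per arm, where both tests are already strong, the gap is 11 to 12 points. There is no false-positive inflation with either test.

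The consequence is limited to one secondary endpoint. It should be corrected because the correction is nearly free, not because the trial's main conclusion depends on it.

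**What to change.** In 2.8, limit the ANCOVA sentence to efficacy variables that have a baseline or screening value. Add one sentence for the global response assessment: compare the groups at week 12 on the five ordered grades, by the Wilcoxon rank sum test or by a proportional-odds model reporting a common odds ratio with its 95% confidence interval. Choose one of the two in advance. Keep the frequencies and percentages by grade, which 2.8 already plans for categorical variables, so that the direction of any difference can be seen.

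The cost is one added sentence and one qualified sentence. Data collection, visit schedule, sample size and primary analysis stay as they are. The trade-off is some loss of sensitivity if the effect is not a consistent shift along the scale; the grade-by-grade table would still show such a pattern.

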### Data management and monitoring

2.9

To ensure data quality, regular monitoring by a contract research organization will be conducted in compliance with standard operating procedures until the end of the study. Experienced clinical research associates will verify source documents and case report forms. All documents related to this trial will be kept confidential in a separate facility, and access to the documents will only be allowed for the purposes of trial management. Data quality will be promoted using double data entry and range checks for data values. A data monitoring committee will not be necessary because the study product is low-risk and no interim analyses will be performed. Auditing is not scheduled for this study.

### Harms

2.10

All adverse events will be recorded in the case report form regardless of causality. The investigator will evaluate the severity of symptoms and determine causal relationship between the study product and the adverse events. If a serious adverse event occurs, the investigator will report to the Institutional Review Board at the earliest and determine whether to continue or stop the trial. Participants will receive financial compensation for injuries found to be due to the study product or procedure.

### Withdrawal and dropout

2.11

Participants may withdraw from the trial at any time for any reason. The investigator may also withdraw participants from the trial due to medical or administrative reasons (adverse events, continuous protocol violations, etc.). Reasons for withdrawal and dropout will be recorded in the case report form.

### Ethics and dissemination

2.12

This protocol (ver. 1.0, issue date 11 Jan 2019) has been approved by the Institutional Review Board of Yonsei University Severance Hospital (approval no. 4-2019-0115) and is registered with Clinical Research Information Service (Identifier: KCT0004286). The trial will be conducted in accordance with the *Declaration of Helsinki* and the Korean Good Clinical Practice guidelines. All participants will be provided detailed information about the trial and the principle investigator will obtain handwritten informed consent from each participant before proceeding with the trial. To protect participants’ identity, subject identification codes will be used instead of participants’ names in all documents. The sponsor and principal investigator will have access to the final dataset. The full protocol and datasets will not be publicized but available from the corresponding author on reasonable request. A model consent form is also available from the corresponding author. Results from this study will be presented at an academic conference or published in a peer-reviewed journal.

## Discussion

3

BPH is a common disease affecting the overall quality of life in industrial countries. Although traditional herbal medicines are widely used to treat LUTS/BPH in Asian countries including Korea, their efficacy remains unclear owing to the poor quality of clinical trials.^[10]^ There is an unmet need to investigate the efficacy and safety of herbal medicines in well-designed and rigorous studies. Herein, we designed the study protocol of the first double-blind, randomized, placebo-controlled trial of HT080 as a single intervention for Korean men with LUTS/BPH.

One of the limitations of this trial is that the treatment duration is 3 months, thus providing short-term outcomes. Furthermore, this study has a relatively small sample size, albeit yielding a statistical power of 80%. The present results will warrant confirmation with further long-term studies with larger sample sizes. Nevertheless, this study has several strengths; it is a prospective study with a double-blind randomized design. In addition, the IPSS questionnaire, the primary efficacy measure of this trial, has been established worldwide as a useful tool to determine the extent of LUTS/BPH, and the validity and reliability of its Korean version has been confirmed.^[22,27]^ We intend to use not only subjective measures (such as IPSS, global response assessment) but also objective measures, such as maximal urinary flow rate and post-void residual volume, to yield outcomes on voiding dysfunction. In addition, our inclusion criterion of an IPSS of 8–19 reflects men with moderate symptoms commonly observed in clinical practice.

In conclusion, this is a first-in-human trial of HT080 in men with LUTS/BPH. The results of this trial will provide high-quality evidence of therapeutic benefit of HT080 for the treatment of LUTS/BPH.
